**List of Abbreviations**

| ACTH | Adrenocorticotropic hormone |
| --- | --- |
| ADCC | Antibody-dependent cytotoxicity |
| AEs | Adverse events |
| APTT | Activated partial thromboplastin time |
| ANC | Absolute neutrophil count |
| BIRC | Blinded independ review committee |
| BMI | Body mass index |
| CA HIV RNA | cell-associated HIV RNA |
| CDC | Complement-dependent cytotoxicity |
| CHB | Chronic hepatitis B |
| CK | Creatine kinase |
| CK-MB | Creatine kinase isoenzyme |
| CRC | Colorectal cancer |
| CRF | Case report form |
| CTCAE | Common Terminology Criteria for Adverse Events |
| CTLA-4 | Cytotoxic T lymphocyte-associated antigen 4 |
| Cys | Cysteine residue |
| dAb | Domain antibody |
| DC | Dendritic cell |
| DLT | Dose-limiting toxicity |
| DOR | Duration of response |
| dMMR | DNA mismatch repair deficienc |
| EC | Ethical Committee |
| ECG | Electrocardiogram |
| FIB | Fibrinogen |
| FT3 | Free triiodothyronine |
| FT4 | Free tetraiodothyronine |
| GC | Gastric cancer |
| GCP | Good Clinical Practice |
| HB | Hemoglobin |
| HBsAg | Hepatitis B surface antigen |
| HCT | Hematocrit |
| HDACI | Histone deacetylase inhibitor |
| HDL | High-density lipoprotein |
| HIV | Human immunodeficiency virus |
| IgG | Immunoglobin G |
| IEC | Independent ethics committeee |
| INR | International normalized ratio |
| L | Lymphocyte |
| LAG-3 | Lymphocyte activating gene-3 |
| ICIs | Immune checkpoint inhibitors |
| LCMV | Lymphocytic choriomeningitis virus |
| LDL | Low-density lipoprotein |
| MSI-H | Microsatellite unstable |
| N | Neutrophil |
| NDA | New drug application |
| NOAEL | No observed adverse effect level |
| ORR | Objective response rate |
| OS | Overall survival |
| PBMCs | Peripheral blood mononuclear cells |
| PD | Progressive disease |
| PD-L1 | Anti-programmed cell death protein 1 |
| PFS | Progression-free survival |
| PLT | Platelets |
| PLWH | People living with HIV |
| PRs | Partial responses |
| PT | Prothrombin time |
| RBC | Red blood cell |
| SD | Stable disease |
| Ser | Serine residue |
| SGOT/AST | Serum aspartate aminotransferase |
| SGPT/ALT | Serum alanine transaminase |
| SIV | Simian immunodeficiency virus |
| T3 | Triiodothyronine |
| T4 | Tetraiodothyronine |
| TdP | Torsades de pointes |
| TEAEs | Treatment-emergent adverse events |
| TIM-3 | T cell immunoglobulin 3 |
| TSH | Thyroid stimulating hormone |
| TT | Thrombin time |
| ULN | Upper limit of normal |
| US | United States |
| VHH | Variable domain of the heavy-chain of heavy-chain antibody |
| WBC | White blood cell count |
| WHV | Woodchuck hepatitis virus |

**Program summary**

| Basic information | Protocol Number: V20220703  Version/Date: V1.3/20220703  Study drug: Recombinant humanized PD-L1 single domain antibody Fc fusion protein injection  Drug code: ASC22 (previously used code KN035, Envafolimab)  Drug specifications: 1 ml: 200 mg (1 ml/ampoule)  Drug production unit: Alphamab Oncology, jiangsu, China |
| --- | --- |
| Title | Anti-PD-L1 antibody ASC22 in combination with chidamide as a “shock and kill” strategy for HIV functional cure: a phase Ⅱ study |
| Study purposes | Assessing whether ASC22 in combination with chidamide can reduce HIV reservoirs in PLWH with virologically suppressed |
| Study design | Single center, prospective, single-arm, phase Ⅱ study |
| Population | PLWH |
| Sample size | This study estimates that 12 participants will complete the trial, and the dropout rate will be controlled within 15%, so 15 participants are planned to be enrolled. |
| Study treatment | Participants received a subcutaneous injection of ASC22 (1mg/kg) once every 4 weeks for a total of 3 times. Chidamide (10 mg) was administered orally twice weekly for 12 weeks, while continue ART |
| Inclusion criteria | (1) Individuals diagnosed with HIV infection;  (2) Age ≥ 18 years old;  (3) BMI ≥ 18.0 to < 35.0 kg/m2;  (4) Capable and willing to comply with the time requirements for study visits and assessments;  (5) Currently receiving ART for at least 24 months, with two consecutive plasma HIV-1 RNA levels <50 copies/ml, separated by an interval of at least 12 months;  (6) During the screening period, CD4+ T cell count is ≥ 250 cells/µl (including the boundary value), and CD4/CD8 ratio is < 0.9;  (7) Agree to use contraception during participation in the project and for up to 6 months after the end of the trial;  (8) Willing to provide informed consent. |
| Exclusion criteria | (1) Those who have suffered from any serious acute illness within 8 weeks;  (2) Subjects with a history of active autoimmune disease or autoimmune disease requiring systemic treatment;  (3) Prior treatment/exposure to any other ICIs (e.g., PD-1, anti-PD-L1, anti-PD-L2, anti-CTLA4, etc.);  (4) Patients who have undergone the following treatments:  a) Received other anti-latent drug treatments within 30 days before enrollment;  b) Underwent radiotherapy or chemotherapy within 30 days before screening;  c) Received immunosuppressive therapy within 60 days before screening;  d) Received immunomodulatory agents (e.g., interleukins, interferons), hydroxyurea, or foscarnet within 60 days before screening;  e) Received an HIV vaccine or systemic cytotoxic chemotherapy within 60 days before screening;  f) Previously received IgG treatment;  g) Underwent blood transfusion or cell growth factor treatment within 90 days before screening;  h) Currently using or planning to use rifampicin, rifabutin, and other drugs during screening;  (5) Individuals whose laboratory examinations meet the following criteria:  a) ANC < 1.50× 109/L; Hb < 105 g/L (for men) or < 95 g/L (for women); platelets < 75× 109/μL; INR > 1× ULN;  b) SGPT/ALT > 1.5× ULN, SGOT/AST > 1.5× ULN, total bilirubin, direct bilirubin > 1.5× ULN, serum creatinine > 1.5× ULN, and the abnormalities are clinically significant;  c) Clinical significance of five thyroid function abnormalities, including T3, T4, FT3, FT4, and TSH;  d) Abnormal epinephrine test with clinical significance, including at least ACTH and cortisol;  e) Abnormal blood glucose and glycosylated hemoglobin tests with clinical significance;  (6) Abnormal and clinically significant findings on the twelve-lead electrocardiogram at the time of enrollment;  (7) Presence of interstitial changes on chest CT examination at the time of enrollment;  (8) Individuals with severe heart disease, symptomatic or asymptomatic arrhythmia;  (9) Patients co-infected with HBV, HCV, syphilis, other liver diseases, and diabetic patients;  (10) Individuals with active or suspected malignant tumors or a history of malignant tumors within the past five years (except for basal cell skin or cervical cancer in situ);  (11) Individuals with a history of tuberculosis or active tuberculosis;  (12) Subjects with psychiatric or substance abuse disorders known to interfere with their ability to meet study requirements;  (13) Individuals who have received immunomodulatory or immunosuppressive treatments (including any dose of IV/oral [PO] steroids, but excluding inhalation, topical, or local injection steroids) within 24 weeks before the first dose of the study drug;  (14) Pregnant and lactating women and individuals, both men and women, who plan to have children during the study;  (15) Individuals with mental health conditions or substance abuse issues that may interfere with the test;  (16) Patients who have used HDACI, such as valproic acid, butyrate, phenylbutyrate, etc., may be enrolled after a 28-day washout;  (17) Patients with severe cardiac insufficiency (New York Heart Association [NYHA] cardiac insufficiency class IV);  (18) Patients with a history of arterial thromboembolic events, including myocardial infarction, unstable angina; cerebrovascular accident, or transient ischemic attack, within six months before enrollment in treatment; standard treatment of uncontrolled hypertension (systolic blood pressure ≥ 150 mmHg or diastolic blood pressure ≥ 100 mmHg); and patients with cardiomyopathy;  (19) Patients with a significant QT/QTC interval prolongation during the screening period (e.g., repeated measurements show QTc interval > 450 milliseconds, or other conditions that may lead to TdP risk, such as heart failure; hypokalemia, familial long QT syndrome) or concurrent use of drugs that may prolong the QT/QTc interval;  (20) Individuals with known allergies or anti-drug antibodies to the drugs or excipients used in this trial;  (21) Individuals deemed unsuitable to participate in this trial by the researcher. |
| Primary outcomes | The primary outcomes were assessed by quantifying changes in cell-associated (CA) HIV RNA, total HIV DNA, integrated HIV DNA in PBMCs, and plasma HIV RNA, as well as by analyzing variations in the functionality of HIV Gag- and Pol- specific CD8+ T cells from baseline to post-treatments. In addition, changes in CD4+ T cell counts, CD8+ T cell counts, and CD4/CD8 ratios were monitored at baseline and at different time points during treatment. |
| Secondary endpoints | The related symptoms and laboratory tests need to be monitored. These symptoms may include vomiting, fatigue, rash, itching, diarrhea, constipation, borborygmi, fever/chills, headache, palpitations, heat sensation, changes in appetite, gastrointestinal pain, gastroesophageal reflux, touch sensitivity, taste and smell disturbances, dizziness, muscle or joint pain, blisters, oral lesions, conjunctivitis, facial edema, and more.  The laboratory tests include blood routine, liver and kidney function, urine routine, myocardial enzymes, blood sugar, blood coagulation, electrolytes, electrocardiogram, chest CT examination, cardiac ultrasound examination, and abdominal B-ultrasound for liver and kidney examination.  The severity of AEs will be graded according to the CTCAE version 6.0. AEs are defined as any adverse medical events occurring in patients or clinical research participants taking a drug product, regardless of causality with the treatment. The investigator will assess the relationship of each event to the study drug as either reasonably likely or not reasonably likely. AEs are divided into grades 1-5, with grade 3 being serious but not life-threatening and requiring hospitalization, grade 4 being life-threatening and requiring hospitalization, and grade 5 indicating an AE-related death requiring immediate intervention. |
| Statistical Analysis | Statistical analyses were carried out using GraphPad Prism 8.0 (San Diego, CA, USA) and SPSS 15.0 statistical software (Chicago, IL, USA). P-value (P) below 0.05 was considered statistically significant. |

**Table 1 ASC22 clinical trial flow chart**

|  | **Screening perioda** | | **Treatment period** | | | | | | **Screening period** | | |
| --- | --- | --- | --- | --- | --- | --- | --- | --- | --- | --- | --- |
| **V1** | **V2** | **V3** | **V4** | **V5** | **V6** | **V7** | **V8** | **V9** | **V10** | **V11** |
| **Screening** | **Baseline** | **Week 2** | **Week 4** | **Week 6** | **Week 8** | **Week 10** | **Week 12** | **Week 16** | **Week 20** | **Week 24** |
| **Visit time** | **Day- 28~Day-2** | **Day 0** | **Day15**  **±2** | **Day 29**  **±2** | **Day 43**  **±2** | **Day 57**  **±2** | **Day 71**  **±2** | **Day 85±2 /Early termination** | **Day 113±5** | **Day 141±5** | **Day 169±2** |
| **Informed consent** | **×** |  |  |  |  |  |  |  |  |  |  |
| **Demographic** | **×** |  |  |  |  |  |  |  |  |  |  |
| **Medical history, treatment history, and history of drug abuse** | **×** |  |  |  |  |  |  |  |  |  |  |
| **Physical examination** | **×** | **×** | **×** | **×** | **×** | **×** | **×** | **×** | **×** | **×** | **×** |
| **Blood pregnancy test**  **(if applicable)** | **×** |  |  | **×** |  | **×** |  | **×** |  |  |  |
| **Height, weight, vital signsb** | **×** | **×** | **×** | **×** | **×** | **×** | **×** | **×** | **×** | **×** | **×** |
| **Blood routined** | **×** | **×a** | **×** | **×** | **×** | **×** | **×** | **×** | **×** | **×** | **×** |
| **Blood biochemistry**  **(including myocardial enzymes)e** | **×** | **×a** | **×** | **×** | **×** | **×** | **×** | **×** | **×** | **×** | **×** |
| **Urine routinef** | **×** | **×a** | **×** | **×** | **×** | **×** | **×** | **×** | **×** | **×** | **×** |
| **Coagulation functiong** | **×** | **×a** | **×** | **×** | **×** | **×** | **×** | **×** | **×** | **×** | **×** |
| **Thyroid functionh** | **×** | **×a** |  | **×** |  | **×** |  | **×** |  |  | **×** |
| **Adrenalinei** | **×** | **×a** |  | **×** |  | **×** |  | **×** |  |  |  |
| **Blood sugarj** | **×** | **×a** |  | **×** |  | **×** |  | **×** |  |  |  |
| **Twelve-lead electrocardiogramc** | **×** | **×** | **×** | **×** | **×** | **×** | **×** | **×** |  |  |  |
| **Chest CT scan** | **×** |  |  |  | **×** |  |  | **×** |  |  |  |
| **Cardiac ultrasound** | **×** |  |  |  | **×** |  |  | **×** |  |  |  |
| **Abdominal ultrasonography (B ultrasound)** | **×** |  |  |  | **×** |  |  | **×** |  |  |  |
| **Plasma HIV Viral load (HIV-1 RNA)** | **×** | |  | **×** |  | **×** |  | **×** |  |  |  |
| **T cell immunek** | **×** | |  | **×** |  | **×** |  | **×** |  |  |  |
| **HIV Gag-specific CD8+T** | **×** | |  | **×** |  | **×** |  | **×** |  |  |  |
| **HIV reservoir**  **(HIV-1 DNA)** | **×** | |  | **×** |  | **×** |  | **×** |  |  |  |
| **ASC22 administration** |  | **×** |  | **×** |  | **×** |  |  |  |  |  |
| **Chidamide dispensing drug** |  | **×** | **×** | **×** | **×** | **×** | **×** |  |  |  |  |
| **Distribute medication diary cards** |  | **×** | **×** | **×** | **×** | **×** | **×** |  |  |  |  |
| **Recycling medication diary cards** |  | **×** | **×** | **×** | **×** | **×** | **×** | **×** |  |  |  |
| **AES** | **×** | | | | | | | | **×** | **×** | **×** |
| **Combination therapy** | **×** | | | | | | | | **×** | **×** | **×** |
| **Summary and analysis of test completion status** |  |  |  |  |  |  |  |  | **×** | | |

a. When the screening test and the day of drug administration coincide, relevant laboratory tests can be shared. Typically, results of pertinent safety tests conducted within approximately one week from the date of signing the informed consent form to the day of drug administration are acceptable.

b. Height measurement is only conducted during the screening period. Vital signs include body temperature, heart rate, respiration rate, and blood pressure.

c. ECG should be performed before ASC22 administration (within ±30 minutes) on the day of drug administration.

d. Blood routine tests include total WBC, WBC differential count (neutrophil [N] absolute count, lymphocyte [L] count, monocyte [M] count, eosinophils [E] count, absolute basophil [B] count), total RBC, HB, PLT, and HCT.

e. Blood biochemistry tests include total protein, albumin, total cholesterol, LDL, HDL, triglycerides, urea nitrogen/urea, uric acid, creatinine, alkaline phosphatase, lactate dehydrogenase, total bilirubin, direct bilirubin, indirect bilirubin, AST, ALT, calcium, phosphorus, magnesium, potassium, sodium, chloride, and serum amylase. Cardiac enzyme spectrum examination includes troponin-I, CK, and CK-MB.

f. Urine routine includes specific gravity, pH, urine sugar, protein, casts, ketone bodies, blood cells, and RBC.

g. Coagulation function includes PT, APTT, INR, FIB, TT, and D-dimer.

h. Thyroid function includes TSH, FT3, FT4, T3, T4. No relevant drug interference exists, and the test results within two weeks of the screening or baseline period are acceptable.

i. Adrenaline testing includes ACTH and cortisol. There is no interference from related drugs, and the test results are acceptable within two weeks of the screening or baseline period.

j. Blood glucose examination includes blood glucose and glycated hemoglobin. The glycated hemoglobin test results within 12 weeks during the screening and baseline periods are acceptable.

k. T-cell immune includes CD3+T cell count, CD4+T cell count, and CD8+T cell count.

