**3.2 Inclusion And Exclusion Criteria**

**3.2.1 Inclusion Criteria**

(1) Individuals diagnosed with HIV infection;

(2) Age ≥ 18 years old;

(3) BMI ≥ 18.0 to < 35.0 kg/m2;

(4) Capable and willing to comply with the time requirements for study visits and assessments;

(5) Currently receiving ART for at least 24 months, with two consecutive plasma HIV-1 RNA levels <50 copies/ml, separated by an interval of at least 12 months;

(6) During the screening period, CD4+ T cell count is ≥ 250 cells/µl (including the boundary value), and CD4/CD8 ratio is < 0.9;

(7) Agree to use contraception during participation in the project and for up to 6 months after the end of the trial;

(8) Willing to provide informed consent.

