(13) Individuals who have received immunomodulatory or immunosuppressive treatments (including any dose of IV/oral [PO] steroids, but excluding inhalation, topical, or local injection steroids) within 24 weeks before the first dose of the study drug;

(14) Pregnant and lactating women and individuals, both men and women, who plan to have children during the study;

(15) Individuals with mental health conditions or substance abuse issues that may interfere with the test;

(16) Patients who have used HDACI, such as valproic acid, butyrate, phenylbutyrate, etc., may be enrolled after a 28-day washout;

(17) Patients with severe cardiac insufficiency (New York Heart Association [NYHA] cardiac insufficiency class IV);

(18) Patients with a history of arterial thromboembolic events, including myocardial infarction, unstable angina; cerebrovascular accident, or transient ischemic attack, within six months before enrollment in treatment; standard treatment of uncontrolled hypertension (systolic blood pressure ≥ 150 mmHg or diastolic blood pressure ≥ 100 mmHg); and patients with cardiomyopathy;

(19) Patients with a significant QT/QTC interval prolongation during the screening period (e.g., repeated measurements show QTc interval > 450 milliseconds, or other conditions that may lead to TdP risk, such as heart failure; hypokalemia, familial long QT syndrome) or concurrent use of drugs that may prolong the QT/QTc interval;

(20) Individuals with known allergies or anti-drug antibodies to the drugs or excipients used in this trial;

(21) Individuals deemed unsuitable to participate in this trial by the researcher.

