**5.2 Test Process**

This project is a prospective, single-center, single-arm clinical trial study. The plan is to enroll 15 PLWH. Following informed consent, each subject will receive a single dose of 1 mg/kg intravenous ASC22 on the first day, followed by a subcutaneous injection of ASC22 (drawing an appropriate volume of ASC22 according to the participant's needs and then injecting subcutaneously, with the injection speed not exceeding 0.06 ml/s). Additionally, oral chidamide intervention will be administered twice a week simultaneously, with a dosage of 10 mg.

Throughout this period, the ART treatment will be continued. The treatment period will last 12 weeks, and follow-up will extend until 24 weeks. Peripheral blood samples will be collected before the ASC22 intervention(every four weeks). Approximately 20 ml of blood will be collected during each session, and subjects will undergo medical evaluation concurrently.

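### Table 1 schedules no pregnancy test at V2, where ASC22 and chidamide are first given, so the only pre-treatment result can be 2 to 28 days old

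*Protocol*

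**What the plan says.** Table 1 of the Protocol lists "Blood pregnancy test" (where applicable) at four visits: V1 (screening), V4 (Week 4), V6 (Week 8) and V8 (Week 12). V2 (baseline, Day 0) is a separate, empty cell in that row.

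The row "ASC22 administration" is marked at V2, V4 and V6. Chidamide is dispensed from V2 onwards, and the Program summary gives the regimen: "Chidamide (10 mg) was administered orally twice weekly for 12 weeks".

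Footnote a to Table 1 lets screening and dosing-day laboratory tests be shared when the two days coincide. It also describes as usually acceptable the "results of pertinent safety tests conducted within approximately one week from the date of signing the informed consent form", counted up to the day of drug administration. Footnotes h and i allow two weeks for thyroid and adrenal results. Footnote j gives a longer limit: "The glycated hemoglobin test results within 12 weeks during the screening and baseline periods are acceptable".

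On eligibility, inclusion criterion 7 (Section 3.2.1) reads "Agree to use contraception during participation in the project and for up to 6 months after the end of the trial". Exclusion criterion 14 (Section 3.2.2) covers "Pregnant and lactating women and individuals, both men and women, who plan to have children during the study". Section 3.2.3.1 lists unexpected pregnancy as a reason for withdrawal. None of these sets a test date, and no other section schedules a pregnancy test on Day 0.

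**The concern.** The protocol treats pregnancy as incompatible with study treatment: it bars entry and is a reason for withdrawal. Yet the visit at which both drugs are started is the only ASC22 visit without a pregnancy test.

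A pregnancy that begins, or first becomes detectable, between the screening test and Day 0 would not be looked for again until V4. By then the participant would have had an ASC22 injection and about four weeks of chidamide. Agreement to use contraception lowers that risk but does not verify status before exposure.

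What is at stake is participant safety. The reservoir, immunology and viral-load endpoints and their analysis are not touched.

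**Working it through.** The plan states no figure to reproduce. The check reads the table row by row and then works out intervals from the visit windows.

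**Is the blank V2 cell real?** Two features of Table 1 suggest it is:
- The viral-load, T-cell, Gag-specific CD8 and reservoir rows have one merged cell across V1 and V2. The pregnancy row does not; V1 is marked and V2 stands alone and empty.
- Seven laboratory rows (blood routine, biochemistry, urine, coagulation, thyroid, adrenal, blood sugar) carry a V2 mark tagged with footnote a. For these a baseline test is the default and a recent result may replace it. The pregnancy row has no V2 mark for a shared result to replace.

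**Inputs (Table 1 header)**
- V1: Day -28 to Day -2
- V2: Day 0
- V4: Day 29±2, so Day 27 to 31
- V6: Day 57±2, so Day 55 to 59
- V8: Day 85±2, so Day 83 to 87
- V1 if footnote a is taken to limit the test to about one week: Day -7 to Day -2 (an assumption about how footnote a is read)

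**Age of the result at first dose** = Day 0 minus test day
- As scheduled: 0 - (-2) = 2 days to 0 - (-28) = 28 days
- Under the footnote a reading: 2 days to 0 - (-7) = 7 days

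**Interval between consecutive tests.** Shortest = earliest later day minus latest earlier day. Longest = latest later day minus earliest earlier day.

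| Interval | Shortest | Longest |
|---|---|---|
| V1 to V4, as scheduled | 27 - (-2) = 29 | 31 - (-28) = 59 |
| V1 to V4, footnote a reading | 27 - (-2) = 29 | 31 - (-7) = 38 |
| V4 to V6 | 55 - 31 = 24 | 59 - 27 = 32 |
| V6 to V8 | 83 - 59 = 24 | 87 - 55 = 32 |
| V2 to V4, if a V2 test is added | 27 - 0 = 27 | 31 - 0 = 31 |

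The interval spanning the start of treatment can reach 59 days, against at most 32 days between later tests. With a V2 test it splits in two, and the on-treatment part (27 to 31 days) falls within the later pattern.

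**Exposure before the V4 test**
- ASC22: 1 of 3 doses (the V2 dose)
- Chidamide: about 2 × 4 = 8 of 2 × 12 = 24 doses

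**Coverage:** 2 of the 3 ASC22 visits (V4, V6) have a same-visit test. With a V2 mark it would be 3 of 3.

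**The case against.** The strongest reply is footnote a. It hangs on the screening-period header over V1 and V2, not only on the rows tagged with it, and a pregnancy test before first dose is naturally a safety test. On that reading the result is at most about 7 days old, and same-day if screening and dosing coincide. The longer limits in footnotes h to j then apply only to the tests they name, and what remains is a wording question.

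This reading is possible, and it is why the range is given both ways. It does not settle the matter:
- The footnote is hedged and permissive. It says which results may be accepted, does not name the pregnancy test, and does not require an older one to be repeated.
- Its coincidence clause cannot operate within the stated windows, because V1 closes at Day -2 and V2 is Day 0.
- With separate limits for thyroid, adrenal and glycated hemoglobin results, a site cannot be sure that one week is the general rule.

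A second reply is that other safeguards exist: contraception, the exclusion of pregnant women and of those planning children, withdrawal on pregnancy, and a physical examination at V2. These reduce the risk or act after the event. None of them tests status on the day treatment starts.

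Three points stand. Exclusion criterion 14 fixes no test date, so this is a gap in the schedule and not a contradiction. The protocol requires no negative result before dosing at V4 or V6 either, so a bare mark at V2 would not by itself prevent exposure; the result-before-dose rule is needed too. And the frequency of the event cannot be estimated from the document.

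**Conclusion.** The point holds. Table 1 permits first dosing with two study drugs on a pregnancy result 2 to 28 days old (2 to about 7 if footnote a is taken to apply). The next test can come as late as 59 days after the screening test, or 38 on the footnote a reading.

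The conclusion rests on the V2 cell being blank as printed and on no other section requiring a Day 0 test.

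The size is limited. The protocol does not say how many of the 15 planned participants the test applies to (range 0 to 15). A V2 test would also not find a pregnancy that first becomes detectable after Day 0; the four-weekly tests cover that. The event may be rare, but the exposure is cheaply avoidable.

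**What to change.** Mark the blood pregnancy test (if applicable) at V2 in Table 1, and state that a negative result must be available before the first dose of ASC22 and of chidamide.

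If a Day 0 test is not wanted, the minimum is a sentence requiring the screening pregnancy test to fall within about 7 days before first dosing and to be repeated if older.

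The cost is one table mark, one assay per applicable participant and a short wait for the result. A separate blood draw should not be needed, since Section 5.2 already says "Peripheral blood samples will be collected before the ASC22 intervention"; a site that takes its V2 safety results from screening should still use that sample for this test.

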**3 Study Design**

**3.1 Basis For Dose Selection**

**3.1.1 Phase I Pharmacokinetic Study**

Phase I studies of ASC22 for tumor indications have received approval in the United States, China, and Japan, respectively. Phase I clinical trials were conducted in 2016 or 2017 with the primary objective of assessing the safety, tolerability, and pharmacokinetic characteristics of ASC22. The study design included a total of 8 dose groups: 0.01 mg/kg, 0.03 mg/kg, 0.1 mg/kg, 0.3 mg/kg, 1.0 mg/kg, 2.5 mg/kg, 5.0 mg/kg, and 10.0 mg/kg, with dosing once a week.

Phase I studies of ASC22 for tumor indications have received approval in the US, China, and Japan, respectively. Phase I clinical trials were conducted in 2016 or 2017 with the primary objective of assessing the safety, tolerability, and pharmacokinetic characteristics of ASC22. The study design included a total of 8 dose groups: 0.01 mg/kg, 0.03 mg/kg, 0.1 mg/kg, 0.3 mg/kg, 1.0 mg/kg, 2.5 mg/kg, 5.0 mg/kg, and 10.0 mg/kg, with dosing once a week.

Currently, pharmacokinetic data for ASC22 in some studies in China and Japan have been collected, revealing the following characteristics. The plasma concentration of ASC22 increases with the dose, and there is no significant variation among participants within the same dose group in the plasma concentration and elimination curve. During repeated dosing, evident drug accumulation is observed from the first to the fifth dose. By the fifth dose, a steady-state concentration of the drug has yet to be reached, and the trend continues to rise. The average elimination half-life of ASC22 in subjects is approximately 200 hours or 8.3 days.

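### Direct adrenal and blood-sugar tests end at Week 12 while the matching thyroid row has a Week 24 test; the rows should be aligned or the shorter safety window stated

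*Protocol*

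**What the plan says.** Table 1 of the protocol has eleven visit columns, V1 (screening) to V11 (Week 24). The three rows at issue begin "Thyroid functionh | × | ×a", "Adrenalinei | × | ×a" and "Blood sugarj | × | ×a"; the letter at the end of each test name is a footnote mark. All three are marked at screening, baseline, Week 4, Week 8 and Week 12. The thyroid row has one more mark, at Week 24. The adrenal and blood-sugar rows are blank at Weeks 16, 20 and 24.

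The footnotes define the tests: "Adrenaline testing includes ACTH and cortisol", and "Blood glucose examination includes blood glucose and glycated hemoglobin".

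The row "ASC22 administration" is marked at baseline, Week 4 and Week 8. The Program summary has chidamide given for 12 weeks. Section 5.2 states: "The treatment period will last 12 weeks, and follow-up will extend until 24 weeks". Table 1 marks adverse events at Weeks 16, 20 and 24. The Program summary names blood sugar among the laboratory tests under the secondary endpoints. Section 3.1.1 gives the pharmacokinetic figure: "The average elimination half-life of ASC22 in subjects is approximately 200 hours or 8.3 days".

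**The concern.** Three endocrine and metabolic tests share a schedule while participants are on treatment and then part company without explanation. Thyroid function gets one value well clear of dosing; ACTH, cortisol, glucose and HbA1c get none after the treatment period.

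Two things are at stake in the safety report. First, an adrenal or glucose abnormality that appears after Week 12 and shows only in the laboratory has no scheduled test that would detect it directly. Second, an abnormality found at Week 12 in a participant who completes the study has no scheduled repeat to show whether it resolved. For these two systems the report could not tell a normal late result from an untested one, while for thyroid it could.

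**Working it through.** **1. Are the blanks real?** Each of the three rows has eleven cells, which map one to one onto V1 to V11. The missing marks are therefore in the schedule and do not come from a broken table.

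**2. Timing of the last direct test.** Inputs from Table 1: last ASC22 dose at V6, Day 57 ± 2; last adrenal and blood-sugar test at V8, Day 85 ± 2; last visit at V11, Day 169 ± 2.

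- Last dose to last test: 85 − 57 = 28 days. With both windows: 83 − 59 = 24 days to 87 − 55 = 32 days.
- Last test to end of follow-up: 169 − 85 = 84 days, about half of the schedule (84/169 = 50%).
- Last dose to the Week 24 thyroid test: 169 − 57 = 112 days.

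**3. ASC22 remaining at the last test.** Half-life from Section 3.1.1: 200 h / 24 = 8.33 days, which reproduces the stated 8.3 days. Fraction of the last dose remaining = 0.5^(days / 8.33).

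| Days since last dose | Half-lives | Remaining |
| --- | --- | --- |
| 24 | 2.88 | 13.6% |
| 28 | 3.36 | 9.7% |
| 32 | 3.84 | 7.0% |
| 112 (Week 24) | 13.44 | 0.009% |

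This assumes simple first-order decline from the day of dosing. Slow absorption from under the skin would leave somewhat more. Chidamide runs for the full 12 weeks, so Week 12 is also the end of its dosing.

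**4. What continues after Week 12?** Table 1 keeps physical examination, weight, vital signs, blood routine, biochemistry, urine, coagulation and adverse-event recording at Weeks 16, 20 and 24. Footnote e itemises the biochemistry panel: it includes sodium and potassium but neither glucose nor cortisol. Footnote f includes urine sugar and ketones. These are indirect signals for the two systems concerned.

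**5. How do the laboratory safety rows compare?** Leaving the pregnancy test aside, there are seven: blood routine, biochemistry, urine, coagulation, thyroid, adrenal and blood sugar. Five reach Week 24; adrenal and blood sugar do not.

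**6. Is a late or repeat test provided for elsewhere?** Section 5.4.5 lists what is checked at each follow-up visit and names no adrenal, glucose or thyroid test. Its provision for abnormal results asks for timely adjustment but sets no retest. Section 3.2.4 requires adverse events to be followed until return to baseline, but is written for participants who leave the study. Neither schedules a value for someone who completes.

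**The case against.** The strongest reply is that nothing in the protocol is contradicted. Section 5.2 says that follow-up lasts 24 weeks, not that every test does, and the Program summary lists blood sugar without timing. In Table 1 the ECG, imaging, viral load and T-cell rows also end at Week 12, so among the specialised tests thyroid is the exception, and it has only one late value, with none at Weeks 16 or 20. All of this stands. The point is an unexplained difference that is cheap to remove, not a contradiction.

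A reader might infer from the Week 24 thyroid test that the protocol itself expects endocrine effects after dosing. No section says so, and a single close-out test does not show it. Nor do adjacent items in exclusion criterion (5) show that the three systems were meant to be one risk group, because the same criterion also covers haematology, INR, liver and renal values.

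A reader might also infer that late adrenal or glucose harm would go wholly unobserved. That is too strong. Symptoms, adverse events, examination, weight, blood pressure, urine sugar and ketones, and electrolytes continue to Week 24. The safety outcome in Section 6 counts drug-related events of Grade 3 or higher, and the protocol describes Grade 3 as needing hospitalisation, so such events would ordinarily come to notice clinically. An unscheduled test is not barred either.

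What remains is the laboratory-only abnormality and the resolution of a Week 12 finding. The continuing items are not direct measurements of either.

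**Conclusion.** The point holds as a modest, inexpensive improvement. As written, the schedule gives no ACTH, cortisol, blood glucose or HbA1c value in the 84 days after the treatment period. The last such values come 28 days (24 to 32) after the last ASC22 dose, with about 10% (7% to 14%) of that dose remaining, and at the end of chidamide dosing. The percentages rest on the average half-life in Section 3.1.1, which comes from the Phase I tumour studies, and on first-order decline.

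The documents do not support saying that late harms will be missed in any particular number, or that the Grade 3 or higher count in Section 6 will be wrong. The protocol does not say when adrenal or glucose effects appear, and the safety experience summarised in Section 3.1.3 mentions none. The number of affected participants is unknown and may be zero. The supportable conclusion is narrower: for these two systems, absence of a late laboratory abnormality could not be claimed from scheduled direct measurements.

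**What to change.** Reconcile the adrenal and blood-sugar rows of Table 1 with the thyroid row and the 24-week follow-up. The simplest way is to collect the same assays (ACTH, cortisol, glucose, HbA1c) at the existing Week 24 visit, where blood is already drawn for blood routine, biochemistry, coagulation and thyroid tests. This would extend direct observation from 28 to 112 days after the last ASC22 dose, and from 0 to 84 days after the treatment period.

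If the assays are not added, give the reason for the difference and state in the safety results that adrenal and glucose findings cover only the period to Week 12.

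The cost is a small schedule amendment and two groups of assays at one visit for at most 15 participants. No extra visit is needed, and no dose, stopping or treatment rule changes.
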